## Design

This clinical trial represents one of the two Randomized Clinical Trials (RCT) of the project “Bottom-up and tOp-down neuromOdulation of motor plaSTicity in cerebral palsy” (BOOST; FRRB 3438840). The study is a randomized, double-blind, sham-controlled pre-post-test study involving 44 children and adolescents with CP. Patients will be treated in pairs, with a matching of motor deficit severity, IQ, or age, by meeting at least two out of these three criteria. Motor severity will be defined on the basis of the Manual Ability Classification System (MACS) level and classified as low to middle (I-II level) or as middle to high (II-III). With respect to age, two group levels will be identified for children (from 6 to 11 years old patients) and adolescents (12–17 years old patients). With respect to IQ, low IQ value (from 50 to 70) and high IQ value (> 71) will be distinguished. Each pair will be randomly assigned to the active or to the sham tVNS group. The randomization will be stratified based on IQ, MACS level, or age. As for the matching within each pair, at least two out of these three criteria must be encountered.

Both groups will undergo a bimanual training in an ecological and highly motivating environment while carrying out bimanual tasks, including recreational play activities during the application of the tVNS protocol. During the training, starting from a set of proposals the choice of the type of activities to be practiced in each session will be left to patients, boosting the motivational aspect of the training. This will also ensure an individualized and goal-directed approach. The therapists will monitor and modify the activities within each pair to ensure that the intervention maintains the quality of the individualized intervention. The positions performed during bimanual tasks and the activities of daily living will be designed to systematically engage postural control of the trunk and lower limbs according to Habit-ILE protocol. The training will be carried out by a therapist with expertise in maintaining the 1:2 ratios. Training activities will be carried out for 5 consecutive days for 3 h/day for 2 weeks (30 h of intervention overall). Children and adolescents will be assessed 1 or 2 days before the start of the treatment (T0), 1 or 2 days after the end of the treatment (T1), and at a follow-up after 3 months (T2).

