## Interventional methods

### Transcutaneous nerve vagus stimulation

Transcutaneous nerve vagus stimulation allows the non-invasive stimulation of the Vagus Nerve by delivering electrical pulses to the sensory afferent fibers of the auricular, thick-myelinated, branch of the vagus nerve in the outer ear. tVNS will be performed by using a CE-marked tVNS device tVNS®E (tVNS, technologies GMBH, Erlangen, Germany). It consists in a programmable stimulation unit connected to two titan ear electrodes that are mounted on a gel frame, allowing to generate and transfer electric impulses from the stimulation unit to the surface of the skin, where the electrodes are applied. The active tVNS will be applied through an active electrode placed on the cymba conchae (innervated by the auricular branch of the vagus nerve), while the sham stimulation will be administered by positioning the active electrode in correspondence of the earlobe, which is free of cutaneous vagus innervation (see Figure 3). Applying active stimulation in both the experimental and control groups, but at differently innervated positions of the ear skin, will allow for sham-control stimulation without hindering blindness to stimulation condition. To avoid cardiac effects, the electrodes will be applied to the left ear. The stimulation intensity will be set based on the perceptual threshold of the participants, corresponding to the perceived intensity and below the perception of pain, in order to make the stimulation tolerable. The device’s stimulation intensity ranges from 0.1 to 5 mA for individuals aged 3 years and older. However, in the present project the stimulation intensity will be constrained to range from a minimum of 0.5 mA to a maximum of 3 mA, falling within the range used in previous tVNS studies with pediatric populations (49). This will limit the risk of any major side effects (e.g., skin irritation) despite any sensorial deficits that may blur participants’ sensitivity to stimulation. In any case, the stimulation will be interrupted if participants would not tolerate the stimulation at the lowest predefined intensity. The intensity of the stimulation will be gradually increased to reach the intensity of stimulation with a ramping-up phase of 30 s. In both active and sham conditions, on (28 s) and off (32 s) periods of stimulation will be alternated, with pulses delivered every 200–300 μs at a frequency of 25 Hz. These are the most common parameters applied in tVNS studies, as outlined in a recent review on parameters settings for neurological and psychiatric disorders (50), and they are the default parameters of the CE-marked tVNS device used in this study. The tVNS, sham or active, will be applied for the first 75 min of the training, every day of the treatment. Given the duty cycle of alternating on and off periods, participants will receive 35 min of stimulation over a 75-min period in each session. Discontinuation to interventions will be contemplated in case of serious adverse effects, withdrawal of consent or significant changes in the participant’s health status, such as the development of any contraindication to the stimulation, that make continuing the intervention unsafe or inappropriate.

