
**Figure 3 fig3:**
[figure not shown]
Schematic depiction of the electrode placements in the active and sham stimulation condition. To deliver active stimulation, the two titanium electrodes are placed on the outer auditory canal of the left ear. For sham stimulation, the two titanium electrodes are positioned on the center of the left earlobe.

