## Statistical analysis

Statistical analyses will be performed using STATISTICA 8.0 (StatSoftInc, Tulsa, Oklahoma). Demographic and clinical variables of the two groups of patients will be inspected through descriptive statistics. Independent sample *t*-test (two-tailed) and χ^2^ will be used to assess the differences between the experimental and control training groups at baseline for continuous and categorical variables, respectively, thus allowing us to verify successful randomization. The outcome measure data will undergo a normal distribution assessment using Kolmogorov–Smirnov tests. If the data adheres to a normal distribution, repeated measures ANOVAs will be employed to analyze differences between treatment group (active vs. sham) and across timepoints (T0-T1-T2) on the primary and secondary outcomes. Duncan *post hoc* tests will be performed to follow-up significant interactions and correct for multiple pair-wise comparisons. Conversely, for data not following a normal distribution, the Kruskal-Wallis H test or Friedman test will be applied. The exploratory analysis will center on investigating sex and age differences in treatment response, considering both primary and secondary outcomes. Furthermore, in light of findings on hemisphere-specific tVNS effects cortical excitability (20) and electrophysiological readiness potentials (52), we will conduct a sensitivity analysis. This analysis will examine potential differences in tVNS effects when administered ipsilateral or contralateral to the side of the most affected limb. Statistical significance will be denoted by *p* < 0.05. As to what concerns missing data, a modified intention-to-treat analysis approach will be adopted, including in the analyses all the participants who had completed the pre- and post-treatment evaluation sessions, even if they had not completed all the training sessions. No imputation of missing data, however, will be used considering the limited sample size and observation points.

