However, an aspect deserving discussion pertains to the tolerability and safety of the stimulation. In general, tVNS is well tolerated and safe in both the pediatric and adult populations. To reduce any possible risks, participants will be thoroughly screened against the defined exclusion criteria to minimize the risks associated with the application of the stimulation. Moreover, to reduce potential effects on the heart, the electrode will be applied to the left ear, whose stimulation does not exert arrhythmic effects (19). The stimulation intensity will be set based on the perceptual threshold of the participants, corresponding to the perceived intensity and below the perception of pain. Setting the intensity below the pain threshold may lead to inconsistent stimulation across participants, resulting in variable outcomes that challenge data interpretation. This constitutes the main limitation of this approach. However, it also helps prevent dropout due to discomfort and promotes adherence to the training regime. Response variability according to inter-individual differences in tVNS responses will be also considered in order to identify best responses to tVNS with respect for example to gender, age and clinical impairments. Even if all recommended procedures will be followed, unwanted side-effects could be experienced by participants. As reported by the systematic review of a total of 51 studies published between the 2007 to the 2017 and involving a total of 1,322 participants (62), the most common effects could include tactile sensations and skin irritation under the electrode. Other less common sensations could include headache, vertigo, nausea, and nasopharyngitis. Very few studies reported cardiac side effects, that were transient and asymptomatic and gastrointestinal side effects. In each case, the occurrence of side effects and the intensity of each sensation will be accurately checked and safety parameters (SpO2 and HR) will be monitored.

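### With every electrode on the left ear, the ipsilateral-versus-contralateral analysis is a subgroup analysis by most affected side; it is not a sensitivity analysis and cannot isolate the relative side of stimulation

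*Protocol article*

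**What the plan says.** After naming exploratory analyses by sex and age, the Statistical analysis section of the protocol article adds a further one. It cites earlier findings that tVNS effects depend on the hemisphere, states "we will conduct a sensitivity analysis", and gives its content as: "This analysis will examine potential differences in tVNS effects when administered ipsilateral or contralateral to the side of the most affected limb".

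The side of stimulation is fixed elsewhere in the same article:

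- Transcutaneous nerve vagus stimulation: "To avoid cardiac effects, the electrodes will be applied to the left ear".
- Figure 3 caption, active arm: "To deliver active stimulation, the two titanium electrodes are placed on the outer auditory canal of the left ear".
- Figure 3 caption, sham arm: "For sham stimulation, the two titanium electrodes are positioned on the center of the left earlobe".
- Discussion: "the electrode will be applied to the left ear, whose stimulation does not exert arrhythmic effects".

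No section provides for the right ear. Under Patient selection, children may have unilateral or bilateral deficits with at least a 25% difference between hands on the Box and Block Test. Either side may therefore be the more affected one.

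**The concern.** The planned contrast is worded as a feature of how tVNS is delivered, and hemisphere-specific stimulation effects are its stated reason. Delivery does not vary in this trial. Only the child's more affected side varies, and that is a baseline characteristic.

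Two things follow.

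- **Interpretation.** If the active-minus-sham difference is larger in one group, the wording invites the conclusion that same-side or opposite-side stimulation works better. The data would fit equally well with a difference due to the affected side itself, the lesioned hemisphere, or anything else that goes with it.
- **Label.** A sensitivity analysis re-examines the main result under other assumptions. This one asks whether the effect differs between types of patient. Under the present name, a reader of the results could take it for a robustness check.

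**Working it through.** **The plan's own figure.** The Sample size calculation states power 0.80 with 22 per group, f(U) = 0.35, alpha 0.05 and numerator DF 2. For the group-by-time interaction under the SPSS-type option:

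- noncentrality = f(U)² × (N − 2) × (3 − 1) = 0.1225 × 42 × 2 = 10.29, with 2 and 84 degrees of freedom
- power = 0.812

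The figure reproduces. It concerns the main comparison, and the article claims no power for the laterality analysis.

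**Aliasing.** Let A = 1 for active and 0 for sham. Let R = 1 if the right limb is more affected and 0 if the left. Let I = 1 if stimulation is ipsilateral to the more affected limb. With the ear always left:

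- I = 1 − R for every child
- A × I = A − A × R

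Both ipsilaterality terms are thus exact combinations of terms already present. A check of design-matrix rank confirms this:

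| Model | Columns | Rank |
|---|---|---|
| Intercept, A, R, A × R | 4 | 4 |
| The same plus I and A × I | 6 | 4 |
| The same four plus ear and A × ear | 6 | 4 |
| Hypothetical layout with both ears crossed with affected side, all terms | 8 | 8 |

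The last row only locates the cause, which is the constant ear; it is not a proposal to change it. No model specified elsewhere could separate the terms, and the result does not depend on sample size.

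**What remains estimable.** A × R is estimable: the active-minus-sham difference in right-affected children minus that in left-affected children. Because sham is also given on the left ear, a purely prognostic difference between left- and right-affected children cancels out of this contrast.

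**Precision, as an illustration.** The article does not give the left/right split, so it is assumed, and the same in both arms. Further assumptions: one outcome measured as change from T0, equal SD in all cells, all 44 children analysed, children treated as independent (the allocation by pairs is ignored), two-sided alpha 0.05, 40 degrees of freedom.

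SE = SD × √(sum of 1/n over the four cells); CI half-width = 2.02 × SE.

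| Split per arm | SE (SD units) | 95% CI half-width | Interaction for 80% power |
|---|---|---|---|
| 11/11 | √(4/11) = 0.603 | 1.22 | about 1.74 |
| 15/7 | √(2/15 + 2/7) = 0.647 | 1.31 | about 1.86 |

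The overall active-sham contrast on the same basis has SE √(2/22) = 0.302, so with an even split the interaction's standard error is twice as large (0.603 / 0.302 = 2.0).

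**The case against.** The strongest defence is that the sentence is accurate as description. With a fixed left ear, each child is stimulated on either the same side as the more affected limb or the opposite side, and the article states the fixed ear openly. It nowhere promises to compare ears. It speaks of tVNS effects, and the Discussion says these are isolated by comparing the two arms, so the natural reading is active versus sham within each affected-side group. That is a reasonable exploratory question and it answers the stated motive: if left-ear stimulation acts differently on the two hemispheres, its benefit may depend on which side is impaired. The neighbouring sex and age analyses are already called exploratory, and the exact model can be left to a fuller document.

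Most of this stands, and it rules out several stronger readings that a reader might infer:

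- **That the analysis merely compares left-affected with right-affected children.** Not so when both arms are used, because sham shares the ear and prognostic differences cancel.
- **That the comparison will be made in the active arm alone.** Nothing in the section says so. Such a comparison would mix in prognostic differences, but this is no ground for criticising the plan as written.
- **That affected side should have been a stratification factor.** Design lists other factors ("The randomization will be stratified based on IQ, MACS level, or age"), but a subgroup variable need not be stratified, and its absence is no fault.

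What the defence does not remove is the label, and the lack of any statement that the contrast and the affected side are the same variable. Low power is common to any subgroup analysis in 44 children and is not in itself an error here.

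**Conclusion.** The point holds as a small correction. By the article's own text, ipsilateral versus contralateral is fully aliased with left versus right most affected limb. This rests only on the fixed left ear and needs no numerical assumption. The analysis is a subgroup (effect-modifier) analysis, wrongly named, and it cannot attribute a difference to the relative side of stimulation as distinct from the affected side or lesioned hemisphere.

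The size of about 1.7 to 1.9 SD for 80% power is illustrative and rests on the assumed splits and the simple model. It shows that a non-significant interaction should not be read as absence of a difference.

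A reader might infer that the analysis is invalid or should be dropped. The documents do not support that: it is a legitimate exploratory estimate if named and read correctly. The primary comparison, the secondary outcomes and the sample size are unaffected.

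**What to change.** Replace the sensitivity-analysis sentences with text such as:

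> As an exploratory subgroup analysis, the interaction between treatment arm and most affected side on change from T0 will be estimated with both arms in the model and reported with a 95% confidence interval. Because the stimulated ear is the same for all participants, the result will be read as effect modification by side of impairment and not as an effect of ipsilateral versus contralateral stimulation.

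If the planned repeated-measures model is kept, the corresponding term is arm by time by affected side. The report should also say that a null result is not evidence of equal effects.

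The cost is wording only: the same data, no added assessment and no change to the stimulation site. The sponsor gives up only a conclusion about relative stimulation side that the design cannot deliver.

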**Methods:**

44 children and adolescents with CP will be involved, treated in pairs in a randomized, double-blind, pre-post test study. The two groups will undergo the Hand-Arm Bimanual Intensive Therapy Including Lower Extremities (HABIT-ILE) for 2 consecutive weeks, with 3 h daily sessions for 5 days per week, for an overall time interval of 30 h; the training will be combined with the application for 75 min/day of active or sham tVNS, in separate, randomly allocated groups. The primary outcome measure will include the scores at the Assisting Hand Assessment and Box and Block Test, and at an *ad-hoc* visuomotor task evaluating manual visuomotor control. Secondary outcomes will include the scores at the Children’s Hand Experience Questionnaire, Canadian Occupational Performance Measure, Melbourne Assessment of Unilateral Upper Limb Function, Gross Motor Function Measure, Vineland, Pediatric quality of life inventory. The evaluation points will include pre (T0), post (T1) and 3-month follow up (T2) assessments. Safety and tolerability will also be assessed.

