
## Sample size calculation

Using the GPower 3 software (51) with the “as in SPSS option” we estimated that, with a mixed design comprising the between group factor (active group vs. sham group) and the within variable (Pre T0-, post T1-, follow-up T2, numerator DF = 2), a sample of 22 subjects per group allows detecting, with a power of 0.80 and an alpha level set at 0.05, a between group difference between active and sham tVNS combined motor training of moderate to large effect size [f (U) = 0.35], which is expected to lead to a clinically-relevant improvement in motor activity and dexterity.

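### The modified intention-to-treat set requires only T0 and T1, but the three-visit repeated-measures ANOVA without imputation would drop any child in it who misses T2

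*Protocol article*

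**What the plan says.** The Statistical analysis section of the protocol article fixes three rules.

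- **Population:** a modified intention-to-treat approach, "including in the analyses all the participants who had completed the pre- and post-treatment evaluation sessions", whether or not all training sessions were completed.
- **Model:** if the data are normal, "repeated measures ANOVAs will be employed to analyze differences between treatment group (active vs. sham) and across timepoints (T0-T1-T2"), for primary and secondary outcomes alike. Otherwise, "for data not following a normal distribution, the Kruskal-Wallis H test or Friedman test will be applied".
- **Missing data:** "No imputation of missing data, however, will be used considering the limited sample size and observation points".

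The visit labels are defined elsewhere. The Methods part of the abstract says "The evaluation points will include pre (T0), post (T1) and 3-month follow up (T2) assessments". The Design section places the later visits "1 or 2 days after the end of the treatment (T1), and at a follow-up after 3 months (T2"). The Sample size calculation uses the same labels, with "the within variable (Pre T0-, post T1-, follow-up T2, numerator DF = 2"), and concludes that "a sample of 22 subjects per group allows detecting" the target effect of f(U) = 0.35 with power 0.80 at alpha 0.05. The Design section adds that PedsQL and VABS-II are given only at T0 and T2.

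**The concern.** Each rule is acceptable alone, but the three do not fit together for a child who attends T0 and T1 and misses the 3-month visit. The population rule counts that child in. The classical ANOVA over three visits cannot use an incomplete set of scores, and the no-imputation rule prevents completing it. The test would then be run on three-visit completers under a modified intention-to-treat label.

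Three things are at stake.

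- An observed T1 score, taken just after treatment, would be discarded because of an absence three months later.
- The exclusion happens after randomisation. If children who respond poorly or tolerate stimulation badly are less likely to return, the group comparison could be biased. T2 matters here because the trial hypothesises a more lasting benefit in the active group.
- The sample size has little slack for lost children.

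If the conflict is settled only once the data are known, the choice between the two sets could depend on the results.

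**Working it through.** **1. Does the stated set require T2?** No. The abstract and the Sample size calculation both equate pre with T0, post with T1 and follow-up with T2. A child with T0 and T1 only is in the stated set.

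**2. Can the named tests use that child?**

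| Test named in the plan | Child with T0 and T1, no T2 |
|---|---|
| Repeated-measures ANOVA, T0-T1-T2 | dropped |
| Friedman over three visits | dropped |
| Kruskal-Wallis at a single visit (T0 or T1) | kept |

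The Kruskal-Wallis route opens only if normality is rejected, so it does not resolve the conflict for the main analysis.

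A simulated data set of 44 children, 4 of them missing T2 only, illustrates the count. It holds 44 × 3 − 4 = 128 scores. The stated set is 44 children. The three-visit complete cases are 40 children and 40 × 3 = 120 scores, so 8 observed scores (four T0, four T1) are discarded. A likelihood-based mixed model used all 44 children and all 128 scores.

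**3. The plan's own sample size.** Inputs from the Sample size calculation: f(U) = 0.35, the SPSS-type effect-size option, two groups, three visits, alpha 0.05. With sphericity assumed, the group-by-time test has

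- λ = f(U)² × (N − 2) × 2
- df1 = 2 and df2 = 2(N − 2)

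At N = 44, λ = 0.1225 × 42 × 2 = 10.29 with df 2 and 84, and power is 0.812. The stated 22 per group reproduces.

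**4. Power at the number complete at T2.** The article gives no T2 loss rate, so the losses below are assumptions.

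| Missing T2 | Complete | λ | df2 | Power |
|---|---|---|---|---|
| 0 | 44 | 10.29 | 84 | 0.812 |
| 1 (2%) | 43 | 10.045 | 82 | 0.802 |
| 2 (5%) | 42 | 9.80 | 80 | 0.791 |
| 4 (9%) | 40 | 9.31 | 76 | 0.768 |
| 6 (14%) | 38 | 8.82 | 72 | 0.743 |
| 8 (18%) | 36 | 8.33 | 68 | 0.716 |

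One lost child still leaves 0.80. Two do not.

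**5. PedsQL and VABS-II.** These have no T1 score, so a three-visit ANOVA cannot be run on them as written. The population rule also lets T1 attendance decide who is analysed for outcomes not measured at T1.

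**The case against.** The strongest reply is that nothing goes wrong if every child returns at T2. The article never says that cases will be deleted; that is a property of the classical method. A reader might infer that the analysed population will certainly differ from the stated one. The documents do not support that, because they give no loss rate. What stands is that the plan has no consistent rule for the first child who misses T2.

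Other stronger readings also go too far.

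- **Power.** A reader might conclude that the trial is seriously underpowered. The loss is modest, and 22 per group can be read as analysable children. A recruitment margin may stand in the full protocol, which a journal article condenses.
- **Children who miss T1 but attend T2.** Leaving them out is a disclosed part of the modified intention-to-treat definition and not a contradiction. T1 falls 1 or 2 days after training, so such cases are probably few.
- **Sphericity.** Uneven visit spacing does not by itself show a violation, and the documents give no epsilon. At N = 44, assumed values from 0.95 to 0.75 would give power from 0.797 to 0.724. That is a separate question, and a correction may be left to the analysis plan.
- **Bias.** The link between poor tolerance and missing T2 is a possibility only. The Discussion says that intensity is kept below pain partly to limit dropout from discomfort. This lowers the risk without removing it.

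One could also read the post-treatment sessions as including T2. That would remove the mismatch, but it conflicts with the article's own visit labels and would openly make the set a completer set.

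**Conclusion.** The concern holds in conditional form. The population rule, the three-visit ANOVA and the ban on imputation cannot all be followed for a child with T0 and T1 but no T2. This is a conflict between rules stated in one section, so a separate analysis plan could settle it only by changing one of them. If 2 to 8 of 44 children miss T2 (assumed), power at the planned effect falls from 0.81 to between 0.79 and 0.72, taking the plan's effect size and sphericity as given. The direction and size of any bias cannot be judged from the documents. The T1 rule and the three-visit model also do not fit PedsQL and VABS-II. This should be fixed, and before unblinding, but the size of the power loss does not make it a fatal defect.

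**What to change.** Replace the repeated-measures ANOVA with a likelihood-based mixed model for repeated measures, with an unstructured visit covariance and small-sample degrees of freedom. Fit it to all randomised children as allocated, using every observed score. This keeps the no-imputation rule and makes the T0-and-T1 attendance condition unnecessary. It relies on scores being missing at random given the observed data. For PedsQL and VABS-II, specify the model on T0 and T2 only. State the power at the number of children expected to have T2.

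At minimum, label the three-visit ANOVA a T0-T1-T2 completer analysis and add a T0-T1 analysis of the full stated set. That removes the inconsistency but not the possible attrition bias.

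The cost is small: revised analysis wording, possibly software other than STATISTICA 8.0, and a stated power that may be slightly lower. Recruitment, visits and treatment do not change.
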